### Sample Size Estimation

Data regarding long-term PEF and FEV1 variability in children and adolescents (with or without asthma) are lacking. Based on lung function variability, data from adults with asthma [14], and assuming a maximum dropout rate of 10%, we estimated that a sample size of 200 children and adolescents (100 in each group) would allow us to detect a difference of at least 1% in PEF or FEV1 coefficient of variation (CV) between healthy participants and participants with asthma, with 90% power at the 0.05 level. Sample size estimation was performed using the G*Power software (version 3.1.6) [15] after assuming a nonparametric distribution of lung function parameters (Wilcoxon rank-sum test).

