### Inclusion and Exclusion Criteria

Inclusion criteria for both cohorts are individuals 6-18 years old; who have access to (or whose parents have access to) a smartphone with internet connection (Wi-Fi or mobile data); and who have given (or whose parents have given) informed, written consent to participate.

Inclusion criteria for the cohort of healthy children and adolescents are no asthma diagnosis or prescription of relevant medication (beta-2 agonists, anticholinergics, inhaled corticosteroids or montelukast) in the last 2 years; and normal baseline spirometry, defined as FEV1 and FEV1/FVC > 80% of predicted (Global Lung Initiative [GLI] normative data [16]) without significant reversibility (FEV1 change < 10%) after administration of 300 μg salbutamol inhaler.

Inclusion criteria for the cohort of children and adolescents with asthma are doctor-diagnosed mild or moderate asthma [2] in the last 2 years; administration of controller therapy for at least 6 months in the previous year; and at least one spirometry, with FEV1 and FEV1/FVC < 80% of predicted (GLI normative data [16]) in the previous year.

Exclusion criteria for both cohorts are major disabilities (eg, chromosome abnormalities, neurological or muscular disorders, neurodevelopmental delay) that may hamper the proper performance of lung function measurements; respiratory conditions (eg, severe respiratory infection, chest trauma) or other health-related events (eg, surgery, trauma) in the month prior to enrollment or during the 3-month period of observation; failure to complete the run-in period successfully (ie, to perform acceptable spirometries at the predetermined time frames); or inability to perform 3 consecutive measurements or 6 measurements in total (3.3% of the anticipated 180 measurements) within the 3-month period of observation.

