### Protocol

Tests will be performed according to American Thoracic Society/European Respiratory Society (ATS/ERS) standards [18]. The technique will be demonstrated by one of the investigators at enrollment, while detailed information will also be available through the online video resources on the study web site [17]. Measurements will be performed twice a day between 7 AM and 9 AM and between 7 PM and 9 PM. Each participant must perform at least 3 technically acceptable maneuvers. Completed measurements will be dispatched by the participants or their parents to a central database via email (encrypted pdf format).

Eligible children and adolescents will initially be asked to complete a run-in period of 10 days (20 trials) to assess their ability to perform technically acceptable spirometries (daily and at predetermined time frames), dispatch the measurements to the central database, and comply to investigators instructions. Those who will demonstrate satisfactory adherence will proceed to the main study consisting of daily measurements at predetermined time frames for a period of 3 months (90 days, 180 trials).

The expected duration of the study is 24 months and it will include two phases: Phase I and Phase II. Phase I will proceed from January 2020 to September 2020 and will consist of assessments of lung function variability in healthy children and adolescents. Phase II will proceed from October 2020 to December 2021 and will consist of assessments of lung function variability in children and adolescents with asthma.

A flow chart of the study is presented in Figure 1. The protocol is in accordance with SPIRIT (standard protocol items: recommendations for interventional trials) guidelines (Figure 2).

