### Variability Analysis

Participant-specific files will be used for variability analysis, focusing primarily on the variability of PEF and FEV1 and secondarily on FEV1/FVC and FEF25-75. All variables will be transformed into percentage predicted values according to GLI normative data [16].

Lung function variability will be assessed in 3 ways: (1) standard variability indices, (2) detrended fluctuation analysis (DFA), and (3) sample entropy (SampEn).

Standard variability indices such as CV (defined as SD divided by the mean) will be used. To avoid any bias due to the presence of trends within the time series, CV will also be calculated as the average of 24 moving windows (length 14 measurements; step 7 measurements).

DFA is a method that has been widely used for the investigation of intrinsic correlation within time series [19]. Initially, the square root of the time series F(*n*) is calculated for segments of different (time) length *n*. A linear relationship in the logarithmic graph F(*n*) - log(*n*) indicates the existence of fractal architecture in the scaling of the specific data, while the slope *a* of the line describes the pattern of long-term fluctuations [19]. A change in daily variability of PEF or FEV1 results in a simultaneous deviation from the predetermined *a* value [6]. This deviation can easily be detected and quantified. It has been shown that the magnitude of *a* deviation reflects the likelihood of asthma exacerbation within the next month [6].

SampEn is a measure of increased irregularity or complexity, which relies on the identification of recurrent patterns within a nonstationary time series (ie, the probability that a series of points within the signal will repeat themselves at a subsequent time-point) [20]. Within a regular and less complex system, the frequency of sequence matches is high; therefore, the entropy is low. SampEn has emerged as a more reliable index of dynamic variability, mainly because it is relatively independent of the length of the time series [20].

Variability analysis will be performed in the MatLab environment.

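### At about 180 readings per child, neither a straight DFA plot nor its slope a can separate fractal long-term structure from ordinary short-memory correlation, so the stated inference is unsupported

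*Protocol article*

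**What the plan says.** The Variability Analysis section of the protocol article names three approaches: standard indices such as the CV, DFA and sample entropy. For DFA, a fluctuation measure F(n) "is calculated for segments of different (time) length" n. The article then makes two interpretive statements. The first is "A linear relationship in the logarithmic graph" of F(n) against n "indicates the existence of fractal architecture in the scaling of the specific data". The second is that the slope a "of the line describes the pattern of long-term fluctuations".

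The length of each series is fixed elsewhere. The Protocol section sets daily measurements "for a period of 3 months (90 days, 180 trials"). The exclusion criteria remove a child who misses "6 measurements in total (3.3% of the anticipated 180 measurements"), so every analysed series stays close to 180 readings.

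The Study Objectives section asks for the pattern of short- and long-term fluctuation in healthy children (objective 1), and for the pattern in asthma and its difference from healthy children (objective 2). The Statistics section contains no step that labels a child or a cohort as fractal.

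**The concern.** A fractal, or long-memory, series has correlations that decay slowly over all time scales. An AR(1) series has correlations that vanish within days. With coefficient 0.5, the correlation at a lag of 10 readings (5 days) is 0.5^10, about 0.001. DFA separates the two only if the plot for the short-memory series visibly bends, and a series of 180 readings offers little range in which to see a bend.

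If the plot looks straight in both cases and the slopes agree, linearity is not evidence of fractal structure and a is not specifically a long-term quantity. Objective 1 could then describe a fractal pattern in healthy children that the data cannot show. Objective 2 could read a difference in day-to-day correlation between cohorts as a difference in long-term structure.

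**Working it through.** **Series length.** Two readings a day for 90 days give 2 × 90 = 180. The moving-window CV, an "average of 24 moving windows (length 14 measurements; step 7 measurements"), agrees: floor((180 − 14)/7) + 1 = 24. The missing-data limit also agrees: 6/180 = 3.3%. The article's own figures therefore reproduce. The sample size of 200 has no bearing on this point.

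**Assumed inputs.** The article gives no segment range, no criterion for linearity and no autocorrelation for PEF or FEV1. Assumed here are 12 log-spaced segment lengths over several ranges, R² cut-offs of 0.90, 0.95 and 0.98, and the process coefficients. The main range is 4 to 45 readings, that is 4/2 = 2 to 45/2 = 22.5 days. It covers log10(45/4) = 1.05 decades.

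**Method.** First-order DFA at N = 180: integrate the series, detrend linearly within each segment, take the root mean square F(n), and regress log F(n) on log n. There were 4000 simulated series per process. The key contrast is AR(1) with coefficient 0.5 (no long memory) against fractional Gaussian noise with H = 0.8 (true long memory).

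| Segments | Process | Mean a (SD) | Median R² | R² ≥ 0.95 | R² ≥ 0.98 |
|---|---|---|---|---|---|
| 4–45 | AR(1) 0.5 | 0.82 (0.08) | 0.980 | 94% | 49% |
| 4–45 | Fractal 0.8 | 0.82 (0.08) | 0.986 | 99% | 73% |
| 6–45 | AR(1) 0.5 | 0.77 (0.09) | 0.975 | 89.8% | 34.8% |
| 6–45 | Fractal 0.8 | 0.80 (0.10) | 0.977 | 94.2% | 41.0% |
| 10–45 | AR(1) 0.5 | 0.71 (0.11) | 0.963 | 71.3% | 13.8% |
| 10–45 | Fractal 0.8 | 0.79 (0.12) | 0.965 | 74.5% | 15.7% |
| 4–90 | AR(1) 0.5 | 0.75 (0.07) | 0.976 | 90.3% | 41.5% |
| 4–90 | Fractal 0.8 | 0.81 (0.08) | 0.988 | 98.5% | 77.5% |

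Repeat runs at 4–45 gave 92 to 94% against 98 to 99% for R² above 0.95.

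**Straightness.** At R² ≥ 0.90 with segments 4–45, 99.8 to 100% of series pass under every process tried. As a discriminator between the two key processes, R² has an area under the ROC curve of 0.64 (4–45), 0.65 (4–60), 0.55 (6–45) and 0.51 (10–45), where 0.5 is chance. A strict cut-off does not rescue the inference. At 0.98 with segments 4–45 it accepts 49% of the short-memory series and rejects 100 − 73 = 27% of the fractal ones.

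**Slope.** At 4–45 the slope separates the two processes no better than chance (area 0.51). In the other ranges AR(1) 0.5 falls 0.03 to 0.08 below the fractal series, which is less than one SD. A somewhat higher AR(1) coefficient closes that gap: at 10–45, coefficients 0.5 and 0.7 give 0.71 and 0.88, which bracket the fractal 0.79.

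**Effect on a cohort comparison.** At 4–45, raising the AR(1) coefficient from 0.3 to 0.7 moves mean a from 0.69 to 1.00 with no long memory present in either case.

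**The case against.** The strongest reply is that this is one explanatory sentence with a citation. It says that linearity indicates fractal structure, not that it proves it, and no test or decision hangs on it. That stands. A reader might infer that nearly every child will be called fractal, but no objective, hypothesis or statistical step classifies anyone. What the plan carries forward is a and its deviation.

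The simulation settings are also assumptions, and the results move with them. At 10–45 only 59 to 85% of noise and short-memory series pass 0.95, and fractal series themselves pass in only 72 to 78%. At 4–90 with a 0.98 cut-off there is some real separation. So it would be too strong to say that the plots are equally straight. It would also be wrong to fault the article for omitting the segment range or cut-off, which a condensed article may leave to the full protocol or SAP.

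White noise is a weak counterexample, because its scaling is genuinely linear and its slope near 0.5 identifies it as uncorrelated. The argument rests on the AR(1) series.

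Finally, long-term need not mean unlimited memory. The Introduction speaks of weeks or months, and segments of up to about 22 days do reach weeks. That is a fair defence of the term if the range is stated with it. It does not defend the fractal inference. Nor does it turn a into a measure of long-term pattern specifically, since short-memory correlation alone moves a.

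**Conclusion.** The point holds as a limit on interpretation. With about 180 readings, a straight DFA plot does not show fractal architecture, and a does not distinguish long-term structure from ordinary day-to-day correlation. Under segments of 4–45, AR(1) 0.5 and fractal noise with H = 0.8 share a mean slope of 0.82, and R² exceeds 0.95 in about 93% against 98% of series. The exact percentages depend on the assumed segments, cut-offs and coefficients. The lack of useful discrimination held across the ranges tried, though separation improves with wide ranges and strict cut-offs.

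A reader might go further and conclude that the DFA comparison between cohorts is invalid. The document does not support that: a can still be compared between healthy children and children with asthma as a measure of correlation. The sample size rests on the CV, and neither the CV nor sample entropy uses DFA, so those parts of the plan are unaffected.

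**What to change.** 1. Delete the inference from linearity to fractal architecture.
2. Describe a as an index of correlation over the segment range used, and state that range in days.
3. Compare a with values from shuffled copies of each series, to show that correlation is present at all.
4. If a fractal or long-memory claim is wanted, test it at cohort level. For each child, find the percentile of a among copies simulated from that child's own AR(1) fit. Average the percentiles over the cohort, and judge the average against the same statistic from simulated AR(1) cohorts. In simulation this mean percentile was about 0.62 to 0.82 for fractal series and 0.49 to 0.57 for noise and AR(1) series. The reference must be simulated rather than set at 0.5, because the null value can itself reach 0.57.
5. Do not use a per-child rule that calls a series fractal when a lies outside its 95% AR(1) range. Truly fractal series fell outside in only 4 to 7% of cases at 4–45, close to the nominal 5%, and in 13 to 23% at 4–90 or 10–45.

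The cost is a short addition to the existing MatLab scripts, with no new data or visits, and possibly a weaker claim. On the article's timetable the asthma phase runs from October 2020 to December 2021, so the wording and the comparison can be settled before objective 2 is analysed.

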## Methods

### Study Objectives and Hypotheses

The first objective of the study (objective 1) is the assessment of lung function variability in healthy children and adolescents, focusing on the range and pattern of short- and long-term fluctuations of PEF and FEV1 and the parameters that may influence them. The second objective (objective 2) is the assessment of lung function variability in children and adolescents with asthma; the pattern of short- and long-term PEF and FEV_1_ variability will be established and the differences from healthy subjects will be defined. Specific changes in the variability pattern prior to exacerbation will also be sought and described (objective 3).

We hypothesize that healthy children and adolescents present normal short- and long-term variability of PEF and FEV1, and that the pattern of variability is influenced by age, sex, and environmental stimuli (season, weather conditions, viral infections, etc). Significant lung function variability is also expected for children and adolescents with asthma; the patterns of variability in children and adolescents with asthma may differ from those observed in healthy children and adolescents, being also influenced by environmental conditions and treatment modalities (controller therapy) in a distinguishable way. Finally, we hypothesize that changes in the pattern of lung function variability occur prior to the loss of asthma control and, thus, may be used to predict the exacerbations of the disease.

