## Discussion

Increased lung function variability correlates with the frequency of respiratory symptoms in the general population [21] and is indicative of poor asthma control in patients with asthma [7-9,14].

Frey et al [6] applied DFA on 300 consecutive PEF values from a cohort of adults with asthma treated in a crossover manner with regular short-acting beta-2 agonists (SABA), regular long-acting beta-2 agonists (LABA), or placebo. They showed that long-term PEF variability was increased in the SABA phase, which meant that there were several periods of decreased lung function (increased vulnerability and high probability of exacerbation). Conversely, PEF variability was decreased during the LABA phase, signifying that lung function remained persistently within normal limits (decreased vulnerability and low probability of exacerbation). Thamrin et al [8] showed that the self-similarity of PEF values over time correlates well with the loss of asthma control within two weeks following the withdrawal of inhaled corticosteroids. Their findings were later corroborated by Kaminsky et al [14] in a large clinical trial of adults with asthma under controller therapy. Thamrin et al [22] have also demonstrated that the probability of asthma exacerbation at the individual level can be estimated by combining the autocorrelation properties of PEF over time with the absolute PEF value at a specific time point, indicating that both are significant for predicting a loss of disease control in the near future.

Regarding SampEn, Veiga et al [23] found that the entropy of airflow time series was reduced in subjects with asthma compared to healthy controls; lower entropy was associated with more severe airflow obstruction (forced oscillations technique) in that study. More recently, Dames et al [24] investigated the entropy of airflow in patients with chronic obstructive pulmonary disease (COPD) and reported that the SampEn of airflow during resting breathing decreased in proportion to the degree of airway obstruction. Similar data in children and adolescents with or without asthma are lacking.

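### The DFA slope deviation is called easy to detect, but within one child (objective 3) splitting the 180 readings gives a chance difference above 0.1 in about half of unchanged children

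*Protocol article*

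**What the plan says.** The Variability Analysis section of the protocol article describes the slope as a summary of long-term fluctuation. It says that a change in daily variability moves the slope away from a predetermined value at the same time, and then: "This deviation can easily be detected and quantified". That sentence has no citation. The sentences on either side cite an adult asthma study, and the second of them links the size of the deviation to the likelihood of an exacerbation in the following month. On the calculation itself, the article says only that the fluctuation function "is calculated for segments of different (time) length".

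The within-child use comes from Study Objectives and Hypotheses: "Specific changes in the variability pattern prior to exacerbation will also be sought and described (objective 3". The accompanying hypothesis is that such changes precede loss of control and could predict exacerbations.

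Each child is measured twice daily "for a period of 3 months (90 days, 180 trials"). The Discussion reports that the cited adult study worked "on 300 consecutive PEF values from a cohort of adults with asthma".

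**The concern.** A change that occurs before an exacerbation, inside a 90-day record, can be seen only by estimating a on part of that record and comparing it with a reference. A DFA slope from a few dozen to a hundred readings has a large sampling error. If that error is of the same order as the deviations being looked for, ease of detection is not a property of this design.

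Objective 3 is what is at stake. Without a measure of chance variation, slope shifts in the weeks before an exacerbation could be described as a warning pattern when children with no exacerbation show shifts of the same size. If the box range is also allowed to change with segment length, a second problem can arise: the short segment can have a systematically different slope from the longer reference.

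**Working it through.** **Inputs from the article**
- Readings per child: 90 days × 2 = 180, which reproduces the stated figure.
- Missing readings: the exclusion limit is "6 measurements in total (3.3% of the anticipated 180 measurements"), and 6/180 = 3.3%. An included series is close to complete, so gaps are ignored here.
- Threshold for a deviation, segment length, box range and detrending order: none stated.

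**Assumptions made here**
- First-order DFA with log-spaced boxes from 4 to N/4 or N/2, where N is the number of readings in the segment.
- Three processes with nothing changing in the child: white noise, AR(1) with coefficient 0.5, and fractional Gaussian noise with H = 0.8.
- Thresholds of 0.1 and 0.2, chosen only to give the noise a scale.
- Monte Carlo simulation, 4,000 series per process.

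**Step 1. Sampling SD of one slope**

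| Readings | SD of a |
|---|---|
| 300 | 0.05-0.07 |
| 180 | 0.065-0.087 |
| 56 (4 weeks × 14) | 0.12-0.17 |

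**Step 2. One slope from all 180 readings.** The normal approximation to the share further than 0.1 from the expected value is 2 × [1 − Φ(0.1/SD)].
- SD 0.065: 2 × [1 − Φ(1.54)] = 0.12.
- SD 0.087: 2 × [1 − Φ(1.15)] = 0.25.

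The simulated share is 13-25%. Over a wider set of log-spaced box ranges starting at 4 or 6, and true slopes from 0.5 to 0.9, it is 12-32%. It reaches 40% with integer-spaced boxes from 4 to 90, and 30-52% only if the smallest box is 10.

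**Step 3. The 180 readings split to look for a change**

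| Comparison in an unchanged child | Difference > 0.1 | Difference > 0.2 |
|---|---|---|
| First 90 against last 90 | 45-58% | 13-24% |
| First 124 against last 56 | 49-65% | 18-37% |

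As a rough check on the second row, the SD of the difference is 0.14-0.19.
- Above 0.1: 2 × [1 − Φ(0.1/0.14)] = 0.48 and 2 × [1 − Φ(0.1/0.19)] = 0.60.
- Above 0.2: 2 × [1 − Φ(0.2/0.14)] = 0.15 and 2 × [1 − Φ(0.2/0.19)] = 0.29.

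This is the same order. The simulated shares are somewhat higher, partly because the mean also shifts when the largest box follows N.

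**Step 4. Length effect.** For AR(1) 0.5 with the largest box at N/4, the mean slope is 0.82 at 180 readings (boxes to 180/4 = 45) and 0.95 at 56 (boxes to 56/4 = 14). With one common box range for both segments the mean shift falls to about −0.01 to −0.02, yet 50-64% of differences still exceed 0.1. Matching the boxes removes the bias but leaves the noise.

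**Step 5. Group level.** With 90 evaluable children per group and an assumed between-child SD of 0.10, the difference detectable with 90% power at two-sided 0.05 is (1.96 + 1.28) × 0.10 × √(2/90) = 0.048, or about 0.05. Sampling error of this size is no obstacle to comparing group means.

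**The case against.** The strongest reply is that the sentence is background on the method and need not refer to segments at all. The abstract describes the aim as defining the normal pattern in healthy controls and detecting departures from it among participants with asthma. On that reading the predetermined value is the healthy pattern, both cohorts supply 180 readings, lengths and boxes can match, and group means are precise enough. That stands, and it is why the point is confined to objective 3.

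Second, the 0.1 and 0.2 thresholds, the splits, the processes and the box ranges are not in the article. That also stands. The percentages are therefore ranges under stated assumptions, and nothing here establishes what size of true change is realistic.

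Third, no alarm rule or individual classification is attached to a: objective 3 is to be sought and described, and the monitoring table tracks adherence and technique only. This limits the harm to interpretation. It does not rescue the sentence, because the hypothesis for objective 3 is that pre-exacerbation change can be used for prediction.

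Fourth, box range and segment length may properly be left to a fuller document. Their absence is not the point. The point is an affirmative statement that the stated series length does not bear out.

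A reader might go further and infer three things that the documents do not support:
- That a slope fitted to all 180 readings is off by more than 0.1 in half of children. Under usual box ranges the share is 12-32%.
- That short segments are necessarily biased. That depends on letting the box range vary with length, which the article does not say will be done.
- That 180 readings are inadequate where the adult study's 300 were adequate. The SDs of 0.065-0.087 and 0.05-0.07 are too close for that contrast to carry much weight.

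**Conclusion.** The concern holds for detection of change within an individual child, and only there. When an unchanged child's series is split, a slope difference above 0.1 arises by chance in roughly 45-58% of children (90 against 90) or 49-65% (last 56 against first 124). A difference above 0.2 arises in about 18-37% for the latter. The claim of easy detection is therefore unsupported for objective 3. Comparison of whole-series slopes between the healthy and asthma groups is not called into question. The sizes depend on the assumed processes, box ranges, splits and thresholds. The conclusion does not depend on 0.1 alone, since chance differences above 0.2 are still common.

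**What to change.** - Remove the word easily, and limit the statement to the within-child search under objective 3.
- In the Phase I healthy children, compute a in segments of one fixed length and one fixed box range (56 readings is one possible length). Take the within-child 95% range of deviations as the noise limit.
- In Phase II, use the same length and box range for both the reference and the pre-exacerbation segments, and call a deviation only outside that limit.
- Report the smallest deviation that can be detected. If it is too large to be useful, restrict a to group-level comparison.

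The timing suits this. By June 2020, 100 healthy children had been enrolled and 74 had completed measurements, and Phase II is scheduled from October 2020, so the limit can be fixed before any asthma data are seen. The cost is a little more analysis work on data already being collected, and a less favourable claim about individual children.
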